## Abstract

**Background:**

Persons with cerebral palsy (CP) are at risk for developing an inactive lifestyle and often have poor fitness levels, which may lead to secondary health complications and diminished participation and quality of life. However, persons with CP also tend not to receive structural treatment to improve physical activity and fitness in adolescence, which is precisely the period when adult physical activity patterns are established.

**Methods:**

We aim to include 60 adolescents and young adults (16-24 years) with spastic CP. Participants will be randomly assigned to an intervention group or a control group (no treatment; current policy). The intervention will last 6 months and consist of three parts; 1) counselling on daily physical activity; 2) physical fitness training; and 3) sports advice. To evaluate the effectiveness of the intervention, all participants will be measured before, during, directly after, and at 6 months following the intervention period. Primary outcome measures will be: 1) physical activity level, which will be measured objectively with an accelerometry-based activity monitor during 72 h and subjectively with the Physical Activity Scale for Individuals with Physical Disabilities; 2) aerobic fitness, which will be measured with a maximal ramp test on a bicycle or armcrank ergometer and a 6-minute walking or wheelchair test; 3) neuromuscular fitness, which will be measured with handheld dynamometry; and 4 body composition, which will be determined by measuring body mass, height, waist circumference, fat mass and lipid profile.

**Conclusions:**

This paper outlines the design, methodology and intervention of a multicenter randomized controlled trial (LEARN 2 MOVE 16-24) aimed at examining the effectiveness of an intervention that is intended to permanently increase physical activity levels and improve fitness levels of adolescents and young adults with CP by achieving a behavioral change toward a more active lifestyle.

**Trial registration:**

Dutch Trial Register; NTR1785

## Background

Cerebral palsy (CP) occurs in 1.5 to 3.0 of 1000 live births and is the most common cause of physical disability in pediatric rehabilitation medicine [1]. Representing a group of permanent disorders of the development of movement and posture, it causes activity limitation that is attributed to non progressive disturbances that occurred in the developing fetal or infant brain [2] which can lead to diminished quality of life, participation and health in adulthood [3-5].

Participation in regular physical activity (PA) provides psychological and physiological benefits in adolescents [6]. In addition, it reduces both the deterioration of mobility-related activities [7] and the development of secondary health problems later in life [8]. However, performing physical activities is often burdensome in adolescents and adults with CP due to reduced muscle mass and inefficient locomotion [9]. This might, together with the distinctly subnormal fitness levels of persons with CP [10], explain why they are at risk of developing an inactive lifestyle. Such an inactive lifestyle has been found in several studies of bilateral spastic CP populations [11-13], but it contrasts with the more active lifestyle of individuals with unilateral spastic CP [14].

Persons develop their adult PA lifestyle in adolescence [15,16]. Therefore, encouraging an active lifestyle and improving physical fitness at this age seems important. Nevertheless, in adolescence and young adulthood, persons with CP tend not to receive structural treatment to improve PA and fitness [17]. A recent review shows that children and adolescents with CP may benefit from exercise programs to improve physical fitness [18]. However, higher fitness levels do not automatically lead to a more active lifestyle [19,20]. Some evidence exists for the effectiveness of interventions aimed at stimulating an active lifestyle through individual counselling in adult populations with physical disabilities in both the short term [21] and long term [22]. It can be speculated that an intervention which combines individual counselling on daily PA with fitness training is ideal to increase PA and improve physical fitness in persons with CP. However, the effectiveness of such an intervention has, to our knowledge, never been evaluated in an adolescent or young adult population with CP.

The LEARN 2 MOVE 16-24 research project aims to evaluate the effectiveness and underlying working mechanisms on the short and long term of an Active Lifestyle and Sports Participation (ALSP) intervention. It is hypothesized that persons following the ALSP intervention will experience increased PA and improved physical fitness in both the short term and the long term (maintenance of effects) as the primary goal of the intervention is to achieve a behavioral change toward a more active lifestyle. The present paper describes the research design, methodology and intervention of the LEARN 2 MOVE 16-24 research project [23-25].

## Methods/design

### Ethical approval

Multicenter approval was granted by the Erasmus MC Medical Ethics Committee, The Netherlands. Local approval was granted by all participating centers.

### Study design

The study has a multicenter randomized controlled design. The experimental group will receive the ALSP intervention. The control group will receive no intervention to improve PA and fitness, which is current policy. Erasmus MC (Rotterdam), Rijndam Rehabilitation Center (Rotterdam), VU Medical Center (Amsterdam), Rehabilitation Center Amsterdam (Amsterdam), Rehabilitation Center De Hoogstraat (Utrecht) and Sophia Rehabilitation (Den Haag/Delft) will participate in this study.

### Blinding

This study has a single-blind research design; all measurements will be performed by assessors who are blind for group allocation and who have no involvement in the recruitment, randomization procedure or intervention.

### Setting

The ALSP intervention and the research measurements will be performed at each participant's house and at two university medical centers and four rehabilitation centers from which all participants will be recruited.

### Sample size

At least 50 participants are required to detect a difference of 30 minutes a day in PA level between the control and experimental group, with a power of 0.8 and an alpha of 0.05. To allow for dropouts, we aim to recruit at least 60 participants. This calculation is based on data from previous research conducted by our research group [13,14].

### Participants

#### Inclusion criteria

Adolescents and young adults with spastic unilateral or bilateral CP are eligible for inclusion if they meet each of the following criteria

• Age 16 - 24 years

• Gross Motor Functioning Classification System (GMFCS [26]) level I-IV

#### Exclusion criteria

Individuals will be excluded if they meet any of the following criteria

• Disabilities other than CP that affect PA or fitness level

• Contraindication for (maximal) exercise

• Severe cognitive disorders and insufficient comprehension of the Dutch language that preclude understanding the purpose of the project and its testing methods

• PA level at baseline exceeds the mean PA level + 2 SD of a CP population

### Recruitment

Each participating center will compile a list of its patients aged 16 - 24 years and diagnosed with CP. All patients will be checked on inclusion and exclusion criteria by their rehabilitation physician. An information letter and invitation to participate was sent to eligible participants. A second letter was sent 3 weeks later to non-responders.

### Randomization

After baseline measurement, participants will be stratified according to their GMFCS level to obtain an equal distribution of gross motor functioning between the two groups. Within each stratum and for each participating center, participants will be randomly allocated (1:1) to the experimental or control group.

### Intervention: Active Lifestyle and Sports Participation

The ALSP intervention lasts 6 months and was developed for adolescents and young adults with physical disabilities [27]. It aims to permanently increase PA and fitness levels by promoting behavioural changes toward a more active lifestyle (EMGO Institute VUmc, Amsterdam, The Netherlands; Health Partners & Io Solutions, Minneapolis, Minnesota, USA) and consists of three parts:

1. Counselling on daily PA

2. Physical fitness training

3. Sports advice

#### 1. Counselling on daily PA

Counselling on daily PA is the main component of the intervention and consists of six individual counselling sessions over a period of 6 months with a PA counsellor (e.g. physical therapist, movement therapist) who serves as a 'personal coach'. During these counselling sessions, participants will receive individual PA advice which primarily focuses on PA in daily life, and not necessarily on sports. The counselling sessions on daily PA are based on Motivational Interviewing (MI) which is defined as a directive, client-centered counselling style for eliciting behavioral changes by helping clients to explore and resolve ambivalence [28]. Techniques that will be applied in the ALSP intervention to invoke the spirit of MI are reflective listening, rolling with resistance, asking open-ended questions, summarizing during a conversation, and showing empathy for the participant. The stages of behavioral change of the Transtheoretical model [29] describe the stages a person experiences when changing his or her health behavior. This model structures the clinical role of MI during the counselling sessions [30]. The first counselling session will last 45 minutes. The five subsequent 20- to 30- minute sessions will be planned monthly. All counselling sessions for a participant will be supervised by the same counsellor. Each participating center will have its own counsellor and all involved counsellors will undertake two days of training to learn the basic principles of MI. The counsellors will also participate in a 1-day follow-up workshop to discuss their initial experiences and refresh their MI knowledge and skills. The first and last counselling session will be sound-recorded for latter analysis to ensure that MI had been applied correctly.

#### 2. Physical fitness training

Physical fitness training will consist of 12 weekly supervised sessions and 12 home sessions. These training sessions of approximately one hour consist of aerobic endurance, aerobic interval and strength training. Over these 12 weeks, aerobic exercise duration and aerobic intensity (as determined by the Karvonen formula [31]) are gradually increased. The peak heart rate (HR), which is required for the Karvonen formula, will be determined during a maximal ramp protocol. The required resting HR will be determined after 5 minutes of rest in a sitting position. During training, HR will be recorded using a Garmin Forerunner 60 heart rate monitor (Garmin Ltd., Olathe, KS, USA). The exercise program starts at a HR of 40% of the heart rate reserve (HRR) on a treadmill, cycle or armcrank ergometer. This will increase to a HR of 80% of the HRR at week 12 [32]. Also, strength exercises of the large muscle groups are included. The training load will be based on a percentage of the baseline 1 repetition maximum (1RM), which is the maximum load that a person can lift once. The training load will begin with one set of 10 to 15 repetitions at 30% of 1RM during week 1 and will increase toward three sets of 15 to 20 repetitions at 75% of 1RM during week 12 [32]. Slight adaptations to these guidelines will be allowed to ensure that the training is both feasible and challenging for each participant. Fitness equipment is available for upper extremities, lower extremities and abdominal muscles. For the training at home, participants will be instructed to perform aerobic exercises (walking/running, cycling, hand-cycling, wheelchair-driving, or swimming) and strength exercises (using Thera-Bands; Hygenic Corporation, Akron, OH, USA) of similar duration and intensity as the supervised training session. HR will also be recorded during home training sessions to evaluate whether participants accomplish the exercise instructions in terms of duration and intensity. After 12 weeks of supervised fitness training the possibilities will be explored to continue the fitness training in the day-to-day environment of each individual.

#### 3. Sports Advice

Sports advice includes sports counselling and sport-specific training. Sports counselling is based on the Rehabilitation & Sports Program [21,22]. During 2 to 4 sessions of approximately 30 minutes, sports history, preferences, possibilities, barriers and facilitators will be identified. This will result in an individualized sports advice, including information on available, accessible and appropriate sports facilities in the person's day-to-day environment. Aspects as transportation, finances, and supervision are also taken into account to ensure long-term benefits. Sport-specific training includes practicing the required skills to perform the sport and ensuring practice opportunities to match sports to each participant's interests and abilities. Examples of the sports to be included in the sport specific training are swimming, soccer, rowing, basketball, climbing, golf, hockey and racket sports. Participation in the sport-specific training sessions will depend on the interests and physical abilities of the participant.

## Measurements

### International Classification of Functioning, Disability and Health

The International Classification of Functioning, Disability and Health (ICF) model provides a unified language and framework for the description of health and health-related states [33]. This model identifies how a health condition, such as CP, can interact with features of the person and the environment to produce three levels of potential disablement: 1) impairments which occur at the level of body structures and functions; 2) activity limitations which occur at the level of performance of tasks or actions by the person; and 3) participation restrictions which occur at the level of participants in their social context. An overview of the ICF model with the parameters to be measured in the present study is shown in Figure 1. The primary outcome measures of this study are the objectively measured PA level, self-reported PA level and physical fitness. All outcome measures will be assessed: at baseline (T0); immediately after completion of the total intervention (6 months, T6) to establish the effectiveness of the ALSP intervention; and at 6 months following the intervention period (12 months, T12) to determine long-term effects. A limited set of outcome measures (physical fitness, health-related quality of life and fatigue) will be assessed after 3 months (T3) to establish the effectiveness of the fitness training of the ALSP intervention. A time schedule of the ALSP intervention and measurements is presented in Table 1. Comparable research equipment will be used in all participating centers.

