**Figure 1 F1:**
[figure not shown]
**ICF model with the outcome measures that will be assessed in this study**. Primary outcome measures are underlined.

**Table 1 T1:** Time schedule of the Active Lifestyle and Sports Participation intervention.

Week	Measurements	Counselling on daily PA	Fitness training Supervised	Home-based	Sports advice
Week 1	Pre-test (T0)	PA session 1			

Week 2			Training 1	Training 2	

Week 3			Training 3	Training 4	Sports session 1

Week 4			Training 5	Training 6	

Week 5		PA session 2	Training 7	Training 8	

Week 6			Training 9	Training 10	

Week 7			Training 11	Training 12	

Week 8			Training 13	Training 14	

Week 9			Training 15	Training 16	

Week 10		PA session 3	Training 17	Training 18	Sports session 2

Week 11			Training 19	Training 20	

Week 12			Training 21	Training 22	

Week 13			Training 23	Training 24	

Week 14	Post-test 1 (T3)				

Week 15		PA session 4			

Week 16					

Week 17					(Sports session 3)

Week 18					

Week 19					

Week 20		PA session 5			

Week 21					

Week 22					

Week 23					

Week 24					(Sports session 4)

Week 25		PA session 6			

Week 26	Post-test 2 (T6)				

Week 52	Follow-up test (T12)				

Note: After 13 weeks the possibility of continuing fitness training in the day-tot-day situation will be explored for each participant

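### The month-3 comparison is assigned to the fitness training, but the design can only estimate the first three months of the whole ALSP programme

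*Protocol article*

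**What the plan says.** Under Measurements (International Classification of Functioning, Disability and Health), the article gives each follow-up visit its own purpose. T6 is for the effectiveness of the ALSP intervention and T12 for long-term effects. T3, at which only physical fitness, quality of life and fatigue are measured, is "to establish the effectiveness of the fitness training of the ALSP intervention". The article therefore distinguishes the package from one of its parts and assigns the part to T3.

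The intervention has three parts: counselling, fitness training and sports advice. On their relative weight, the counselling section states: "Counselling on daily PA is the main component of the intervention".

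The Study design section describes two groups: "The experimental group will receive the ALSP intervention", and "The control group will receive no intervention to improve PA and fitness, which is current policy". Under Randomization there is one allocation step, after baseline: "participants will be randomly allocated (1:1) to the experimental or control group". No group receives training without the other parts.

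Table 1 puts T3 in week 14. Counselling sessions 1, 2 and 3 fall in weeks 1, 5 and 10. The first sports session is in week 3, and "Sports session 2" is in week 10.

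**The concern.** A randomised comparison supports a causal claim about whatever differs by design between the arms. At T3 that is more than the training. The experimental arm has also had about half of the part the article calls its main one, plus sports advice. The purpose given to T3 is therefore narrower than the contrast that the trial can estimate.

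This matters because physical fitness is a primary outcome and the Background section says the project also aims to study working mechanisms. If the T3 result is reported under its present purpose, one component is credited with an effect that the trial can attribute only to the combination. This is not a detail left to a statistical analysis plan. The objective and the design are both stated in the article, and they do not match.

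**Working it through.** The plan gives no figure of its own to reproduce on this point. The check is a count of what is scheduled before T3, followed by a comparison of the estimand with the arms available. The sample size plays no part.

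**Inputs**
- T3 in week 14, and the weeks of all sessions: Table 1.
- Counselling: six sessions, the first of 45 minutes and five of 20 to 30 minutes (section on counselling).
- Training: 12 supervised and 12 home sessions of about one hour (section on fitness training).
- Sports counselling: 2 to 4 sessions of about 30 minutes (section on sports advice). Sessions 3 and 4 are bracketed in Table 1, in weeks 17 and 24.

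**Sessions before week 14**

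| Component | Weeks before T3 | Delivered by T3 | Control arm |
|---|---|---|---|
| Training | 2 to 13, two per week | 24 of 24 | 0 |
| Counselling | 1, 5, 10 | 3 of 6 | 0 |
| Sports counselling | 3, 10 | 2 of 2–4 | 0 |

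**Counselling minutes before T3, as a share of all counselling minutes**
- Follow-up sessions of 20 minutes: (45 + 2 × 20) / (45 + 5 × 20) = 85 / 145 = 59%.
- Follow-up sessions of 30 minutes: (45 + 2 × 30) / (45 + 5 × 30) = 105 / 195 = 54%.

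**Training as a share of scheduled session time before T3**
- Training: 24 × 60 = 1,440 minutes. Sports counselling: 2 × 30 = 60 minutes.
- With 85 minutes of counselling: 1,440 / (1,440 + 85 + 60) = 1,440 / 1,585 = 91%.
- With 105 minutes of counselling: 1,440 / (1,440 + 105 + 60) = 1,440 / 1,605 = 90%.

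Table 1 does not date the sport-specific training described under sports advice. Further exposure of that kind before T3 is possible but cannot be counted.

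**Estimand against design.** Write T for training, C for counselling sessions 1–3 and S for sports sessions 1–2.
- The randomised T3 contrast is: mean outcome under T + C + S, minus mean outcome under none.
- An effect of training would be either (T alone minus none) or (T + C + S minus C + S).
- The first needs an arm with T alone and the second an arm with C + S alone. The trial has neither, and there is no second randomisation that would create one.

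The training effect equals the T3 contrast only if C and S add nothing by T3, either directly or through the training, for example by improving adherence to the home sessions. That is an assumption which the randomisation cannot test. Physical activity level, the outcome that counselling is meant to change, is not in the T3 measurement set. Even a non-randomised adjustment for activity at T3 is therefore unavailable.

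**The case against.** The strongest reply is that the sentence mainly explains why a visit sits in week 14. The training block ends in week 13, and the measures chosen are those that training should move. The abstract, the hypothesis and the Discussion all concern the combined intervention, and the Statistics section specifies no component analysis. Training accounts for about 90% of scheduled time before T3 and is graded in intensity, whereas counselling is aimed mainly at everyday activity. It is reasonable to expect training to drive most of any change in aerobic capacity and strength.

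Much of this stands. The timing of T3 is sensible, and the expectation about aerobic capacity and strength is plausible. It is weaker for quality of life and fatigue, which counselling could plausibly affect too. But time share is not effect share, and plausibility is not identification. The article also words the purposes of T3 and T6 differently, so the T3 wording is more than a scheduling remark.

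A reader might infer more than the documents support:
- **That training's share of the T3 effect could be anything from 0 to 100%.** This only restates that the share is not identified. It is not a plausible range, given the scheduled exposures.
- **That the T3 result will lead centres to adopt training alone, or that T3-to-T6 changes will be read as training versus counselling.** The article proposes neither. Its Background points the other way: it notes that better fitness need not bring a more active lifestyle, and it favours a combination.
- **That the trial has no information at all on training exposure.** Heart rate is recorded in supervised and home sessions, which gives non-randomised information. The article proposes no dose-response analysis, so there is none to relabel.
- **That all the other sessions run alongside the training.** Counselling session 1 is in week 1, and training starts in week 2.

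**Conclusion.** The point holds as a mismatch between a stated objective and the design. By T3 the experimental arm is scheduled to have had 24 of 24 training sessions, 3 of 6 counselling sessions (54–59% of the minutes) and 2 sports sessions, against nothing in the control arm. The T3 difference is a valid estimate for that package and not for the training component. No later analysis plan can separate the two by randomisation.

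The conclusion rests on Table 1 being followed as printed and on the two-arm design. The 90–91% time share also takes sessions at their stated approximate lengths and leaves out the undated sport-specific training.

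The importance is moderate. The error limits what may be concluded at one intermediate visit, for one primary outcome domain (physical fitness) and two secondary ones. The T6 and T12 comparisons of the package with control are unaffected, and no number in the plan changes.

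**What to change.** Restate the T3 objective as: the effect on physical fitness, health-related quality of life and fatigue of the first three months of the combined ALSP programme, including the completed training block, versus no intervention. Add one sentence saying that T3 results will not be attributed to the training component alone.

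The cost is wording only. Visits, measurements, sample size, allocation and treatment stay as they are.
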